### Gastrointestinal bleeding

If gastrointestinal bleeding occurs, with stool occult blood (++ or higher), hematemesis, or fresh blood in stool, close observation should be strengthened. For those diagnosed with upper gastrointestinal bleeding, fasting should be enforced, and acid suppression, gastric mucosal protection, and hemostasis (such as tranexamic acid, Lysteda, etc.) should be administered; octreotide may be used if necessary. For those with lower gastrointestinal bleeding, active hemostatic measures and supportive symptomatic treatment should be provided; if bleeding cannot be controlled, surgical intervention may be necessary.

### Proteinuria

If there are two consecutive instances of urine protein (++), a 24-hour urine protein quantification should be performed.

- Grade 1: Urinary protein 1+, or < 0.3 g%, or < 3 g/L.
- Grade 2: Urinary protein 2~3+, or 0.3~1.0 g%, or 3~10 g/L.
- Grade 3: Urinary protein 4+, or > 1.0 g%, or > 10 g/L.
- Grade 4: Nephrotic syndrome.

### Diarrhea

When subjects experience diarrhea of grade 2 or higher, appropriate measures such as antidiarrheal treatment and rehydration should be taken.

- Grade 1: Daily bowel movements exceed pre-treatment < 4 times;
- Grade 2: Daily bowel movements exceed pre-treatment 4~6 times, intravenous rehydration < 24 hours;
- Grade 3: Increase of ≥ 7 times/day or incontinence; intravenous treatment ≥ 24 hours; hospitalization;
- Grade 4: Life-threatening secondary symptoms.

### Elevated bilirubin

If grade 2 or higher elevation of bilirubin occurs, the physician may determine appropriate management measures based on the patient's condition.

- Grade 1: > 1.5 × ULN;
- Grade 2: > 1.5~3.0 × ULN;
- Grade 3: 3.0~10.0 × ULN;
- Grade 4: > 10.0 × ULN.

### Elevated transaminases

If grade 2 or higher elevation of transaminases occurs, the investigator may determine appropriate management measures such as liver treatment based on the subject's condition.

- Grade 1: > 3.0 × ULN;
- Grade 2: > 3.0~5.0 × ULN;
- Grade 3: > 5.0~20.0 × ULN;
- Grade 4: > 20 × ULN.

## Management of special adverse events for recombinant humanized anti-PD-1 monoclonal antibody

### Infusion-related reactions

Clinical symptoms of infusion-related reactions include fever, chills, nausea, itching, vascular edema, hypotension, headache, bronchospasm, urticaria, rash, vomiting, muscle pain, drowsiness, or hypertension. Severe reactions may include acute respiratory distress syndrome (ARDS), myocardial infarction, ventricular fibrillation, and cardiogenic shock. Therefore, subjects in this study must be closely monitored for related clinical symptoms. Guidelines for the management of infusion-related reactions are shown in Table 2, and the management of allergic reactions can be referred to in [Appendix Seven](#_附录).

In the event of a severe reaction, continuous electrocardiographic monitoring and the administration of rescue medications (including but not limited to adrenaline, corticosteroids, antihistamines, bronchodilators, and oxygen) are required for resuscitation. If infusion-related reactions or suspected events of CTCAE grade 2 or higher occur, infusion of recombinant humanized anti-PD-1 monoclonal antibody must be immediately stopped. During the first intravenous infusion of recombinant humanized anti-PD-1 monoclonal antibody, subjects' vital signs must also be monitored within 30 minutes after the end of the infusion. Subjects will be informed of the possible delayed symptoms following infusion and will be asked to contact their study physician if such symptoms occur.

If a severe allergic reaction occurs, subjects must be treated according to local best medical practices. If a subject experiences a CTCAE grade 2 or higher infusion-related reaction again, the subject must immediately discontinue the treatment permanently and withdraw from the study.

**Table 2: Treatment Adjustment Guidelines for Infusion-related Reactions**

| **CTCAE Grade** | **Adjustment Measures** |
| --- | --- |
| Grade 1: Mild | - Transient mild reaction; interruption of infusion and clinical intervention are not recommended. Reduce the infusion rate by 50% and closely monitor for any worsening symptoms. - Clinical intervention as necessary |
| Grade 2: Moderate | - Suspend Recombinant Humanized Anti-PD-1 Monoclonal Antibody Treatment, and immediately provide systemic treatment (e.g., antihistamines, NSAIDs, analgesics, intravenous fluids); When infusion-related reactions are relieved to grade 0-1, re-administer the treatment and reduce the infusion rate by 50%. - Closely monitor for any worsening symptoms during this period. - Take appropriate therapeutic intervention measures according to local medical practices. |
| Grade 3: Severe | - Immediately stop the infusion and remove the infusion line; the investigator will decide whether to re-administer based on the subject's actual condition. - If re-administering, during subsequent treatments, the infusion time should be at least 2 hours, and relevant prophylactic medications (such as diphenhydramine and NSAIDs) should be given, while closely monitoring for clinical symptoms related to infusion-related reactions. - Take appropriate therapeutic intervention measures according to local medical practices. |
| Grade 4: Life-threatening and requires urgent clinical intervention | - Subjects who experience grade 4 infusion-related reactions must immediately discontinue the medication permanently and withdraw from the study. - Take appropriate therapeutic intervention measures according to local medical practices. |

Abbreviation: NSAID = Non-Steroidal Anti-Inflammatory Drug.

### Severe allergic reactions

Antibody administration may cause allergic reactions. Therefore, it is crucial to provide appropriate medications and medical equipment to treat acute allergic reactions immediately, and researchers must be trained to recognize and manage allergic reactions. Research sites must be equipped with emergency rescue teams and equipment, as well as the capability to admit subjects to intensive care units if necessary. In the event of a severe allergic reaction, subjects must receive emergency treatment immediately according to local relevant diagnostic and therapeutic protocols. Subjects must be administered epinephrine and dexamethasone immediately, and continuous cardiac monitoring should be initiated; consideration may be given to obtaining serum IgE specimens. Subjects must permanently discontinue the study treatment and withdraw from the research. Subjects experiencing such symptoms must immediately inform the investigator.

**Allergic Reaction**

The National Institute of Allergy and Infectious Diseases (NIAID) and the Food Allergy and Anaphylaxis Network (FAAN) define an allergic reaction as a severe allergic reaction that occurs rapidly and may lead to death. These three types of allergic reactions cover 80% (Type 1) to 95% of cases (all three types).

1. Acute allergic reactions (ranging from minutes to hours) involve the skin, mucous membranes, or both (for example, widespread urticaria, itching or flushing, swollen lips or tongue), and at least one of the following conditions is present:
2. Difficulty breathing [for example, dyspnea, wheezing - bronchospasm, wheezing, decreased peak expiratory flow (PEF), hypoxemia];
3. Decreased blood pressure or symptoms of related end-organ dysfunction (for example, hypotensive shock, syncope, incontinence).
4. After exposure to allergens (for a few minutes to several hours), the patient may experience two or more of the following conditions:
5. Involvement of skin and mucosal tissues (e.g., extensive urticaria, itching, swelling of the lips and tongue);
6. Difficulty breathing (e.g., dyspnea, wheezing - bronchospasm, wheezing, decreased PEF, hypoxemia);
7. Decreased blood pressure or related symptoms (e.g., hypotensive shock, syncope, incontinence);
8. Persistent gastrointestinal symptoms (e.g., abdominal pain, vomiting).
9. Blood pressure decreases in patients after exposure to known allergens (within minutes to hours):
10. Infants and children: systolic blood pressure low (age-specific) or systolic blood pressure decreases below 30%;
11. Adults: systolic blood pressure below 90 mmHg or a reduction of more than 30% from baseline.

### Immune-related adverse events (irAE)

Recombinant humanized anti-PD-1 monoclonal antibody may be associated with the following significant irAEs: immune-related liver dysfunction, interstitial lung disease, pancreatitis, endocrine disorders [hypothyroidism (for replacement therapy of hypothyroidism, see [Appendix 8](#附录十) ), hyperthyroidism], and immune-related hyperglycemia.

In addition, irAEs also include the following clinically significant potential events: exfoliative dermatitis, pigmentary retinopathy, arthritis, myocarditis, hemolytic anemia, partial seizures that may occur in subjects with inflammation in the cerebral hemispheres, adrenal insufficiency, myasthenia gravis, optic neuritis, and rhabdomyolysis.

For suspected irAEs, close monitoring of the relevant system functions is required, and a thorough evaluation should be conducted to determine the cause and exclude other reasons. Overall, based on the severity of the events, it may be necessary to suspend or permanently discontinue the recombinant humanized anti-PD-1 monoclonal antibody and/or provide symptomatic treatment, such as corticosteroids. When administering 1-2 mg/kg of prednisone or a glucocorticoid with equivalent efficacy, a gradual dose reduction should begin after the event has been alleviated to grade 0-1. If the irAE remains at grade 0-1 at this time, re-administration of recombinant humanized anti-PD-1 monoclonal antibody therapy should be considered. In the event of an irAE of grade 3 or higher (excluding endocrine system diseases), immediate permanent discontinuation of the drug and withdrawal from the study is required.

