**Sintilimab injection:**

Throughout the study, dose adjustments for sintilimab are not permitted; the principles for pausing and permanently discontinuing sintilimab administration are outlined in Table 1.

If a subject experiences a grade 2 drug-related irAE or a grade 3 or higher other AE (refer to the ESMO guidelines for the management of toxicity related to immune checkpoint inhibitors), the subject must suspend administration, with a maximum delay of 7 days; subsequent administration schedules will be adjusted accordingly. If the administration is delayed for more than 7 days, it will be considered a missed dose, and the subject will receive the next cycle of administration according to the original schedule (calculated from the date of the first administration). If treatment-related adverse reactions have not recovered to grade 0-1 or baseline levels within 6 weeks after the last dose of Sintilimab, then Sintilimab should be permanently discontinued. If a subject discontinues the medication for more than 6 weeks and the investigator determines that the risks of continuing administration outweigh the benefits, they may permanently withdraw from the study treatment.

If a subject requires a gradual reduction in dosage of steroids due to an adverse event, the recombinant humanized anti-PD-1 monoclonal antibody may be discontinued for a longer period until the steroid tapering is completed or reduced to a prednisone dose of ≤10 mg/day (or equivalent dose). If the discontinuation exceeds 6 weeks (with the maximum discontinuation time for sintilimab due to steroid tapering not exceeding 12 weeks), the investigator may reassess the overall risk-benefit evaluation before resuming the use of the recombinant humanized anti-PD-1 monoclonal antibody.

Subjects may interrupt administration for reasons other than toxic reactions (such as surgical procedures), with the interruption not exceeding 6 weeks. The investigator may restart the use of recombinant humanized anti-PD-1 monoclonal antibody *based on an overall risk-benefit assessment.*

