**Table 1 Sintilimab Dose Adjustment Scheme**

| Sintilimab-related adverse events | Severity | Dose adjustment |
| --- | --- | --- |
| Pneumonia | Grade 2 | Suspend administration ^a^ |
|  | Grade 3 or 4 or recurrent Grade 2 | Permanent discontinuation |
| Diarrhea/Colitis | Grade 2 or 3 | Suspend administration ^a^ |
|  | Grade 4 | Permanent discontinuation |
| Hepatitis | For subjects with baseline normal ALT, AST, or TBIL, a 2nd grade increase in AST, ALT (3-5 times ULN) or TBIL (1.5-3 times ULN); For subjects with baseline AST, ALT, or TBIL > ULN, an increase in AST, ALT, or TBIL ≥ 50% (meeting the 2nd grade requirement) and a duration of < 7 days. | Suspend administration ^a^ |
|  | For subjects with baseline normal ALT, AST, or TBIL, a 3rd or 4th grade increase in AST, ALT (> 5 times ULN) or TBIL (> 3 times ULN); For subjects with baseline AST, ALT, or TBIL > ULN, an increase in AST, ALT, or TBIL ≥ 50% (meeting the 3rd or 4th grade requirement) and a duration of ≥ 7 days. | Permanent discontinuation |
| Nephritis | Grade 2 or 3 elevation of serum creatinine | Suspend administration ^a^ |
|  | Grade 4 elevation of serum creatinine | Permanent discontinuation |
| Endocrine diseases | Symptomatic Grade 2 or 3 hypothyroidism  Grade 2 or 3 hyperthyroidism  Grade 2 or 3 pituitary inflammation  Grade 2 adrenal insufficiency  Grade 3 hyperglycemia or Type 1 diabetes | Suspend administration ^b^ |
|  | Grade 4 hypothyroidism  Grade 4 hyperthyroidism  Grade 4 pituitary inflammation  Grade 3 or 4 adrenal insufficiency  Grade 4 hyperglycemia or type 1 diabetes | Permanent discontinuation |
| Dermatological adverse reactions | Grade 3 | Suspend administration ^a^ |
|  | Grade 4, Stevens-Johnson syndrome (SJS) or toxic epidermal necrolysis (TEN) | Permanent discontinuation |
| Thrombocytopenia | Grade 3 | Suspend administration ^a^ |
|  | Grade 4 | Permanent discontinuation |
| Other immune-related adverse reactions | Grade 3 or 4 elevated amylase or lipase  Grade 2 or 3 pancreatitis  Grade 2 myocarditis ^c^  Other immune-related adverse reactions of grade 2 or 3 occurring for the first time | Suspend administration ^a^ |
|  | Grade 4 pancreatitis or any grade of recurrent pancreatitis  Grade 3 or 4 myocarditis  Grade 3 or 4 encephalitis  Other immune-related adverse reactions of grade 4 occurring for the first time ^d^ | Permanent discontinuation |

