| Recurrent or persistent adverse reactions | Recurrent grade 3 or 4 (excluding endocrine disorders)  Grade 2 or 3 adverse reactions within 12 weeks after the last administration  Not improved to grade 0-1 (excluding endocrine disorders)  Corticosteroids failed to reduce to ≤ 10 mg/day of prednisone equivalent within 12 weeks after the last administration. | Permanent discontinuation |

a: Resume administration after symptom improvement to grade 0-1 or baseline level.

*The safety of reinitiating Sintilimab treatment after myocarditis improves to grade 0-1 is still unclear.

b: Pituitary inflammation, adrenal cortical insufficiency, hypothyroidism/thyroid dysfunction, and type 1 diabetes can be re-administered when adequately controlled and requiring only physiological hormone replacement therapy.

c: The safety of resuming treatment with this product after myocarditis improves to grade 0-1 is still unclear.

d: For grade 4 laboratory abnormalities, the decision to discontinue medication should be based on accompanying clinical symptoms/signs and according to the clinical judgment of the investigator.

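### Section 8.4.3 orders a permanent stop and study withdrawal for non-endocrine grade 3 immune-related events that Table 1 tells the site to suspend and then resume

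*Protocol*

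**What the plan says.** Section 8.4.3 ends its advice on irAEs with a mandatory rule. For "an irAE of grade 3 or higher (excluding endocrine system diseases), immediate permanent discontinuation of the drug and withdrawal from the study is required". Only endocrine disease is excepted, and the sentence does not distinguish a first event from a recurrence.

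Section 5.3, under sintilimab, states that "the principles for pausing and permanently discontinuing sintilimab administration are outlined in Table 1". At grade 3, Table 1 suspends rather than stops for diarrhea/colitis, nephritis (creatinine elevation), skin reactions and pancreatitis. It also suspends for "Other immune-related adverse reactions of grade 2 or 3 occurring for the first time". Grade 3 or 4 amylase/lipase elevation is suspended too, and is listed under the same heading of other immune-related reactions. Footnote a, attached to all of these, reads "Resume administration after symptom improvement to grade 0-1 or baseline level".

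Table 1 has a separate row for recurrent or persistent reactions. It stops sintilimab for recurrent grade 3 or 4 events outside the endocrine group. It also stops for an entry that runs over two lines: "Grade 2 or 3 adverse reactions within 12 weeks after the last administration", followed by "Not improved to grade 0-1 (excluding endocrine disorders". The body text of section 5.3 and the Protocol Summary set a shorter limit. Sintilimab stops for good if treatment-related reactions have not recovered to grade 0-1 or baseline within 6 weeks of the last dose. Section 5.3 lets a hold for steroid tapering run to at most 12 weeks.

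Three places allow the remaining drug plus HAIC to continue after one drug is stopped for toxicity, if the investigator expects benefit: the note to the dose adjustment scheme in the Protocol Summary, section 4.3.2 item 3, and the note at the end of section 5.3.

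**The concern.** The two rules give opposite orders for the same patient. After a first grade 3 immune-related colitis that settles to grade 0-1, Table 1 directs the site to give the checkpoint inhibitor again, and 8.4.3 forbids it. A site that resumes as Table 1 says breaches 8.4.3. A site that stops as 8.4.3 says departs from the table designated for that decision. Read literally, 8.4.3 also ends donafenib and HAIC for a patient whom other sections would let continue.

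Patient treatment, sintilimab exposure and the count of discontinuations for adverse events therefore depend on which section the investigator reads.

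**Working it through.** The plan gives no figure to reproduce, so the check sets the provisions side by side.

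**Step 1: first grade 3 event, judged immune-related, not endocrine.**

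| Event | Section 8.4.3 | Table 1 with footnote a |
| --- | --- | --- |
| Diarrhea/colitis | Permanent stop, withdraw | Suspend, resume on recovery; stop at grade 4 |
| Nephritis | Permanent stop, withdraw | Suspend, resume on recovery; stop at grade 4 |
| Skin reaction | Permanent stop, withdraw | Suspend, resume on recovery; stop at grade 4, SJS or TEN |
| Pancreatitis | Permanent stop, withdraw | Suspend, resume on recovery; stop at grade 4 or any recurrence |
| Other first-time irAE | Permanent stop, withdraw | Suspend, resume on recovery; stop at grade 4 |
| Amylase/lipase elevation | Permanent stop, withdraw | Suspend at grade 3 or 4, resume on recovery |
| Pneumonia, myocarditis, encephalitis | Permanent stop, withdraw | Permanent stop |
| Hepatitis, normal baseline | Permanent stop, withdraw | Permanent stop |

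The first five rows and amylase/lipase conflict. The last two rows agree on stopping sintilimab.

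**Step 2: does other text settle it?** The body of section 5.3 orders suspension for a grade 2 irAE and for other adverse events of grade 3 or higher. It is silent on a grade 3 irAE. Section 5.3 designates Table 1, but does not say that Table 1 overrides 8.4.3, and the 8.4.3 rule does not refer to Table 1.

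**Step 3: time allowed for recovery.**

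- Section 8.4.3: none.
- Section 5.3 and the Protocol Summary: 6 weeks after the last dose. Section 5.3 allows up to 12 weeks for steroid tapering.
- Table 1, persistent-reaction row: 12 weeks after the last dose.

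**Step 4: withdrawal.** The Protocol Summary requires withdrawal from study treatment when both drugs are permanently stopped for adverse reactions. Section 8.4.3 requires it when one is.

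**Step 5: what is left uncovered if 8.4.3 defers to Table 1.** For a baseline above ULN, the hepatitis row suspends for a rise "meeting the 2nd grade requirement) and a duration of < 7 days" and stops for "an increase in AST, ALT, or TBIL ≥ 50% (meeting the 3rd or 4th grade requirement) and a duration of ≥ 7 days". A grade 3-4 rise lasting under 7 days has no explicit hepatitis entry.

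Whether eligible patients can reach that cell depends on the grading rule, which the row does not state for abnormal baselines. As an assumption, apply the ULN multiples that Table 1 gives for normal baselines (section 8.3.7 has the same transaminase threshold):

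- AST/ALT up to 5 × ULN is eligible (section 4.1). A 50% rise from 4 × ULN gives 4 × 1.5 = 6 × ULN, above the 5 × ULN threshold for grade 3. Any baseline above 5/1.5 = 3.33 × ULN does the same.
- Bilirubin up to 2 × ULN is eligible. A 50% rise from that ceiling gives 2 × 1.5 = 3.0 × ULN, so any larger rise passes the 3 × ULN threshold.

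**Step 6: the same pattern for donafenib.** Section 5.4.5 item 4 requires study withdrawal after an investigator-recommended stop of more than 2 weeks. For toxicity not recovered within 2 weeks, section 5.3 and the Protocol Summary permanently stop only donafenib. The provisions cited above then allow sintilimab plus HAIC to continue.

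**The case against.** The best reconciliation is that the 8.4.3 sentence means recurrence. It directly follows a sentence on re-administration, and its endocrine exception mirrors the one in Table 1's recurrence row. That may be what was intended, but the sentence sets no such limit. Elsewhere the protocol states recurrence when it means it, as in the infusion-reaction rule of section 8.4.1 and in Table 1 itself. If recurrence was meant, the sentence still needs correcting.

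A second argument is that section 5.3 designates Table 1, so a careful reader would follow it. This has weight and is why the fix aligns 8.4.3 to the table. It does not cancel a mandatory order in a safety section.

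Third, Table 1 is headed by relation to sintilimab, not by immune mechanism, and diarrhea and skin toxicity are known donafenib effects (section 1.3.2). This stands: those entries conflict only where the event is judged immune-related. The same holds for grade 3 thrombocytopenia, which Table 1 also suspends.

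Fourth, section 3.4 counts any irAE of grade 3 or higher as a DLT, so the strict rule may be the intended one. The Protocol Summary also lets the investigator stop sintilimab for intolerable toxicity, so stopping is defensible. This too stands: choosing between the rules is a clinical decision.

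On hepatitis, section 5.3's suspension rule or Table 1's residual entry for first-time grade 2 or 3 irAEs might be argued to cover the short grade 3 rise. The defensible statement is therefore that the hepatitis row lacks an explicit entry, not that the protocol is silent.

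**Conclusion.** The contradiction is real and should be fixed. For five Table 1 entries and amylase/lipase elevation, a first grade 3 event judged immune-related gets opposite mandatory instructions. The study-withdrawal order also conflicts with three provisions on continuing the other drug. This rests on taking the 8.4.3 sentence as written.

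Some stronger readings are not supported:

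- A reader might infer that the response rate or follow-up is distorted. No effect on ORR is shown. Section 4.3.3 provides continued follow-up after early withdrawal from study drug, and the analysis is descriptive and single-arm.
- A reader might infer that Table 1 gives a flat 12 weeks to recover. Section 5.3 and the Protocol Summary set 6 weeks for unrecovered treatment-related reactions.
- A reader might infer that permanent discontinuation is the natural entry for the short hepatitis rise. That would make the 7-day threshold in the row meaningless for grade 3-4 rises.
- A reader might want a number of patients affected. The protocol gives no irAE rate for this regimen, so none can be derived.

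**What to change.** Replace the last sentence of 8.4.3 with: *For irAEs of grade 3 or higher, suspend or permanently discontinue sintilimab according to section 5.3 and Table 1, including the 6-week non-recovery limit; if sintilimab is permanently discontinued, donafenib plus HAIC may continue under section 4.3.2 item 3, and efficacy and survival follow-up continue.*

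Before this is adopted, the clinical lead should confirm that rechallenge after a recovered first grade 3 irAE is intended, because the change relaxes a mandatory stop. The clinical lead should also set the Table 1 instruction for grade 3-4 AST, ALT or bilirubin rises lasting under 7 days from a baseline above ULN. No default is proposed here.

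As a secondary change, limit section 5.4.5 item 4. When donafenib is stopped for toxicity not recovered within 2 weeks, only donafenib is permanently discontinued, and sintilimab plus HAIC may continue. This should not turn every donafenib stop of more than 2 weeks into a permanent one, because section 5.3 reserves that for unrecovered toxicity.

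The cost is wording in three places, two clinical decisions and an amendment through the ethics committee (section 11.1). No patients, visits or procedures are added.
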